## Demographic and baseline characteristics

Demographic and baseline characteristics of all patients in the FAS will be analyzed.

The primary efficacy analysis will be performed on the MITT set.

### Demographic characteristics, medical history and diagnoses

All demographic characteristics and all medical history data will be presented.

### Previous treatments

All previous treatments will be listed by patient with the associated ATC codes for the WHO drug dictionary.

Descriptive statistics will be produced to analyze the previous treatments by therapeutic class as defined in Section 7.1.

### Baseline efficacy variables

Categorical variables (binary, nominal and ordinal) will be summarized by contingency tables (frequencies and percentages),

Quantitative variables will be summarized by their mean, standard deviation, standard error, median, quartiles and range, minimum and maximum values.

### Baseline safety variables

All safety variables will be presented. Baseline data are defined as the last available data before the start of IMP infusion.

All laboratory data except those defined as efficacy variables (in the above section) or as exploratory variables will be defined as safety criteria. All laboratory data will not be displayed in the baseline section but in the analysis of safety in order to display in the same table the baseline and other data.

In addition, the frequency, grade, and attribution of surgical complications to the neoadjuvant treatment will be described using the Clavien-Dindo classification (to grade surgical complications).

## IMP and concomitant medications

### Extent of exposure

Summary tables will display the number of patients exposed, duration of exposure (in minutes, automatically derived from the start and end times of IMP infusion/injection), total volume (mL) and total administered dose (g) to which each patient was exposed.

### Concomitant medications

All concomitant medications will be listed by patient with their ATC codes.

Descriptive statistics will be produced to analyze the Concomitant medications by therapeutic class as defined in Section 7.2.

A particular attention will be paid to:

- - Anti-emetics
  - Oxaliplatin
  - Leucovorin
  - Fluorouracil (infusion)

## Efficacy analysis

### Primary efficacy variable(s)

- - 1. ***Description of the primary efficacy variable***

The primary endpoint is the proportion of patients who achieve a pathologic complete response, defined as no viable tumor cells on the resected specimen, in the MITT set.

The primary efficacy variable is a dichotomous variable (yes/no) that will be summarized using a proportion.

- - - 1. ***Hypothesis Test and Primary Analysis Model***

A Simon’s two-stage optimal design will be applied with the following hypothesis:

- H0: p (pCR) ≤0.16
- H1: p (pCR) ≥0.35

If 2 or less patients achieved pCR in the first stage with 13 MITT patients, the study will be stopped, otherwise another 23 MITT patients will be added to the study (stage 2) and the results of the 36 MITT patients will be analyzed at the end of the study. If overall 10 or more patients achieved pCR, then the null hypothesis will be rejected with a type I error of 0.05.

In addition, the one-sided 95% confidence interval (Wilson Score method) of the percentage of patients with pCR will be estimated for all patients in the MITT set and the PP set.

- - - 1. ***Multiple comparisons and interim analyses***

Interim analysis will be done upon recruitment of the first 13 MITT patients to assess the futility and efficacy of the study.

### Secondary efficacy variable(s)

#### *Description of the secondary efficacy variable*

The secondary efficacy variable are listed in Section 10.1.

#### *Analysis of secondary efficacy variables*

Mainly, PFS will be estimated using Kaplan Meier methods. Median PFS and the PFS rate at 3 years and corresponding 95% confidence intervals will be presented. PFS will be defined for all patients regardless of their pCR as the time between the date the patient is enrolled in the study and the date the disease progression is shown on imaging or the date of death whatever is earlier and the last follow up date in the absence of disease progression or death. Patients without progression or death will be censored at the last assessment regarding progression. PFS will be analyzed for the ITT, the MITT and the PP set.

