|  |  |  |  |  |  |  |  |  |  |  |  |  |
| **Physical / clinical examination** |  |  |  |  |  |  |  |  |  |  |  |  |
| Vital signs | x |  |  | x | x | x | x | x | x |  | x | x |
| Weight | x |  |  | x | x | x | x | x | x |  | x | x |
| Pelvic MRI (rectal protocol) | x |  |  |  |  |  |  |  |  | x |  |  |
| CT scan or PET of the chest and the abdomen | x |  |  |  |  |  |  |  |  |  |  |  |
|  |  |  |  |  |  |  |  |  |  |  |  |  |
| **Laboratory tests** |  |  |  |  |  |  |  |  |  |  |  |  |
| Hematology tests (CBC) | x |  |  | x | x | x | x | x | x | x |  |  |
| Biochemistry tests* | x |  |  | x | x | x | x | x | x | x |  |  |
| Urine or serum pregnancy test** | x |  |  | x |  | x |  | x |  | x |  |  |
| Free T4 and TSH¥ | x |  |  |  |  | x |  |  |  | x |  |  |
| Tumor markers (CEA and CA 19-9) | x |  |  |  |  |  |  |  | x |  | x | x |
| PT and PTT |  |  |  |  |  |  |  |  |  | x |  |  |
| Hepatitis B virus surface antigen, Hepatitis C virus antibodies | x |  |  |  |  |  |  |  |  |  |  |  |
| HCV polymerase chain reaction  (PCR) for patients positive for HCV antibodies (to differentiate active infection from past infection with HCV) | x |  |  |  |  |  |  |  |  |  |  |  |
|  |  |  |  |  |  |  |  |  |  |  |  |  |
| **Pathology assessment** |  |  |  |  |  |  |  |  |  |  |  |  |
| Sigmoidoscopy |  |  | x |  |  |  |  |  |  |  |  |  |
| PD-L1 expression on Tumor and Immune Infiltrating T cells & CD4+, CD8+ and CD3+ T cell infiltration† | x |  | x |  |  |  |  |  |  | x |  |  |
| Microsatellite instability‡ | x |  | x |  |  |  |  |  |  |  |  |  |
| Tumor Regression Grading |  |  |  |  |  |  |  |  |  | x |  |  |
|  |  |  |  |  |  |  |  |  |  |  |  |  |
| **Treatment** |  |  |  |  |  |  |  |  |  |  |  |  |
| Prior treatments | x |  |  |  |  |  |  |  |  |  |  |  |
| Radiotherapy 25 Gy in 5 fractions |  | x |  |  |  |  |  |  |  |  |  |  |
| Concomitant medications (mFOLFOX-6 and anti-emetics) |  |  |  | x | x | x | x | x | x |  |  |  |
| Other concomitant medications |  |  |  | x | x | x | x | x | x | x | x | x |
| Surgery TME (open, laparoscopic or robotic) |  |  |  |  |  |  |  |  |  | x |  |  |
| Achievement of a pathological complete response after surgery |  |  |  |  |  |  |  |  |  | x |  |  |
|  |  |  |  |  |  |  |  |  |  |  |  |  |
| **IMP administration** |  |  |  |  |  |  |  |  |  |  |  |  |
| Avelumab premedication |  |  |  | x | x | x | x | x | x |  |  |  |
| Avelumab 10 mg/Kg every 2 weeks (6 cycles) |  |  |  | x | x | x | x | x | x |  |  |  |

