- - 1. Prior to surgery: pelvic MRI (rectal protocol), optional
    2. Frequency, grade, and attribution of surgical complications to the neoadjuvant treatment using the Clavien-Dindo classification (to grade surgical complications).
    3. Laboratory tests:
    - Hematology assessments: CBC
    - Coagulation tests (PT and PTT) should be done a couple of days prior to surgery on week 16 or 17
    - Blood chemistry: BUN, creatinine, electrolytes, SGPT, SGOT, GGT, alkaline phosphatase, bilirubin
    - Urine or serum pregnancy test for women of childbearing potential who are sexually active
    1. Concomitant medications
    2. Adverse event collection
    3. Surgery: TME (open, laparoscopic, or robotic):
    - All TME procedures will be video recorded and the corresponding videotapes and images of the resected specimens are to be made available.
    - Centralized random audit of videos will be performed (Curtis NJ et al., 2017).
    1. Quality assessment and completeness in a TME specimen: all TME specimens are to be processed and graded using the recommendations of the College of American Pathologists (CAP, 2013; Parfitt JR et al., 2007).
    - Specimen handling upon receiving:
      - Paint the non-peritonealized bare areas of the specimen with ink.
      - Open the specimen along the anterior aspect from the top and the bottom, leaving the bowel intact at a level just above and just below the tumor.
      - Place loose, formalin-soaked gauze wicks into the unopened ends of the bowel.
      - Fix the specimen for at least 48 hours.
    - Fixed specimen:
      - Slice through the unopened rectum at 3–5 mm intervals; lay slices down on the work surface.
      - Inspect these slices to note:
        - Extent of tumor and the closest distance of tumor to the CRM (circumferential radial margin, record this distance).
        - Any obviously positive nodes and the distance of any positive node to the CRM (record this distance).
        - Record whether the closest distance of tumor to CRM is anterior, posterior or lateral.
        - Fat away from the tumor must also be examined to detect lymph nodes.
    - Block selection for microscopic examination:
      - Three blocks of tumor showing closest CRM.
      - Two blocks of tumor showing luminal aspect.
      - All lymph nodes (being careful not to double-count nodes present in more than one slice).
      - Any polyps.

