### 8.2.6. Follow-up visits: every 3 months after surgery

The procedures to be done every 3 months for 3 years after surgery are as follows:

- - 1. Physical examination/vital signs/weight
    2. Laboratory tests:
    - Tumor markers (CEA and CA 19-9)
    1. Concomitant medications
    2. Adverse event collection
    3. Patient-reported outcome: quality of life assessment using FACT-C questionnaire
    4. Patient survival status
    5. Disease Status

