## General rules for handling of missing or inconsistent data

No replacement of missing data will be performed except for:

- - 1. The primary efficacy endpoint is a dichotomous criterion (yes/no). A missing primary endpoint will be considered as if the endpoint is not fulfilled (no pCR).
    2. The duration would be based on the time difference between the date the patient signs the informed consent and is enrolled in the study and the date of progression of disease on imaging. Otherwise, if the patient’s disease did not progress, the patient will be censored in the analysis and the last follow-up date or date of last communication with the patient will be applied instead.

All estimated or replaced data will be edited along with a flag in the statistical appendices.

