**Indemnity**

Participation in this study will not entail any financial compensation to patients. Only-trial specific procedures will be covered by the Principal Investigator while the standard of care will be paid by the patient.

Trial-specific procedures:

1. Pre-treatment and on-treatment thyroid function tests
2. Pre-treatment and on-treatment pregnancy test
3. Virology testing
4. Experimental pathology assessment (day 10 post-radiation): sigmoidoscopy + biopsy + pathology analysis
5. Avelumab administration

Standard of care:

1. Pre-treatment imaging: MRI/endoscopic ultrasound/CT or PET-CT scan
2. Pre-treatment biopsy
3. Pre-treatment laboratory tests: CBC, biochemistry, tumor markers (CEA, CA 19-9)
4. Radiotherapy
5. mFOLFOX-6 chemotherapy with supportive anti-emetics and insertion of vascular access device
6. Surgical TME (or abdominoperineal resection if TME is not possible)
7. Follow-up laboratory tests and imaging

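### Three-year PFS counts progression only when imaged, but no follow-up scan is timed and the event and censoring rules conflict, so the estimate is unreliable in either direction

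*Protocol*

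**What the plan says.** **Event.** Section 12.8.2 measures PFS from enrolment to "the date the disease progression is shown on imaging or the date of death whatever is earlier". Section 12.5 measures the duration to "the date of progression of disease on imaging" and does not mention death.

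**Censoring.** For a patient who has not progressed, Section 12.5 says "the last follow-up date or date of last communication with the patient will be applied instead". Section 12.8.2 first names the last follow-up date, then adds: "Patients without progression or death will be censored at the last assessment regarding progression". That assessment is not defined.

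**Imaging.** Section 8.2 presents Table 1 as the full list of assessments. Its row "CT scan or PET of the chest and the abdomen" is marked at the inclusion visit only, and Sections 8.3.1 and 10.2 agree. The one later scan with a stated time is in Section 8.2.5: "Prior to surgery: pelvic MRI (rectal protocol), optional".

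**Follow-up visits.** Section 8.2.6 opens with "The procedures to be done every 3 months for 3 years after surgery are as follows". It lists examination with vital signs and weight, tumour markers, concomitant medications, adverse events, FACT-C, survival status and disease status. Section 8.2.7 repeats the list for the final visit. Neither includes imaging, and neither says how disease status is determined.

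**Standard of care.** Section 17 (Indemnity) lists "Follow-up laboratory tests and imaging" among procedures the patient pays for. It gives no modality, interval or criteria.

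**The concern.** The endpoint depends on a measurement that the protocol does not schedule. The assessments it does schedule after surgery cannot produce a progression event. A recurrence seen at endoscopy, proven by biopsy or felt on examination enters PFS only when a scan is done or the patient dies. The recorded event date then reflects when somebody ordered a scan.

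The censoring text adds a second problem. Where scans are frequent and regular, last scan and last contact are close together and the choice matters little. Where scans are sparse and untimed they can be years apart, and the choice decides which way the estimate moves.

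The proportion progression-free at 3 years is the first secondary objective (Section 2.2), and Section 9.2.3 expects it to rise relative to historical controls. An SAP can choose between the censoring rules. It cannot create visit procedures or recover scan dates that were never collected.

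**Working it through.** **Plan's own figure.** There is none to reproduce. The protocol gives no event count, power or precision for PFS. The Simon design concerns pCR only and is not affected.

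**The two statements side by side**

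| | Section 12.5 | Section 12.8.2 |
|---|---|---|
| Progression | imaging only | imaging only |
| Death | not mentioned | event |
| Censoring date | last follow-up or last communication | last follow-up date, and also last assessment regarding progression |

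**Assumptions for size (not from the documents).** Event times are exponential with true 36-month PFS of 0.50, and nobody is lost before month 40 (surgery at about month 4 plus 3 years). The 0.50 is a round value; Section 1.1 quotes a 3-year DFS near 50%, which is a different endpoint.

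**Case A: event-free patients censored at last contact.** If every event is recorded d months late, apparent 36-month PFS is S(36 − d) = 0.50^((36 − d)/36):

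- d = 3: 0.50^(33/36) = 0.530
- d = 6: 0.50^(30/36) = 0.561
- d = 12: 0.50^(24/36) = 0.630

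A Kaplan-Meier simulation of 200,000 patients with exponentially distributed delays of the same means gave 0.528, 0.564 and 0.634. The formula delays deaths as well as progressions. Deaths are not delayed by missing scans, so for a given delay these values lie at the high end.

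If instead a fraction f of progressions is never imaged, apparent PFS is 1 − (1 − f)(1 − 0.50). This is 0.55 for f = 0.10 and 0.60 for f = 0.20. The bias is upward.

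**Case B: event-free patients censored at their last scan.** Detection delays are the same. Patients with an imaged event stay in the analysis until that event. Event-free patients leave early, so the risk set shrinks selectively. Simulated 36-month PFS:

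| Mean delay (months) | One scan per event-free patient, random time | Half of event-free patients never scanned after baseline |
|---|---|---|
| 3 | 0.30 | 0.19 |
| 6 | 0.32 | 0.21 |
| 12 | 0.36 | 0.25 |

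The bias is downward, and large.

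**Sensitivity to the true value.** With true PFS of 0.70, Case A gives 0.72 to 0.79 for the three delays, and 0.73 or 0.76 with 10% or 20% of progressions never imaged. Case B gives 0.34 to 0.55.

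**Regular assessments for comparison.** On a fixed grid that includes month 36, at 3-, 6- or 12-month spacing, the simulation returns 0.50 for true 0.50 and 0.70 for true 0.70. More generally, the estimate equals true PFS at the last assessment before month 36. With three-monthly visits counted from surgery at about month 4, that visit falls at about month 34, and 0.50^(34/36) = 0.52. The residual error is about 0.02.

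**The case against.** The strongest reply is that imaging is foreseen. Section 17 lists it as standard of care, and the three-monthly examination, tumour markers and disease status give clinicians a regular prompt to order a scan. PFS is a descriptive secondary endpoint with no hypothesis or sample size behind it. All of this stands. The accurate description is imaging foreseen but neither timed nor standardised, not imaging absent.

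A reader might infer four stronger claims that the documents do not support:

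- **That 3-year PFS is biased upward because unscanned patients count as progression-free.** This holds only if they are censored at last contact or at a disease-status visit. If the last assessment regarding progression means the last scan, they leave the risk set early and the bias runs the other way.
- **That the delays in Case A correspond to particular scan intervals.** They do not. A regular grid that includes month 36 gives no bias at that time point. The delays stand for ad hoc detection and are assumptions.
- **That scans will be missed at some sites or by patients who cannot pay.** Section 17 says who pays. Nothing shows that scans would be omitted.
- **That a formal comparison with a 50% benchmark is spoiled.** The protocol sets no PFS benchmark. The figure near 50% is DFS, and one source cited for it concerns, by its title, fixed cT3 or cT4 tumours, whereas this trial excludes T4. Comparability is limited whatever the scan schedule.

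The central point remains: the endpoint accepts only imaging, the visit schedule does not provide it, and the two sections give different rules.

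**Conclusion.** The point holds in this form. Three-year PFS is not reliably estimable from the protocol as written, and the direction of error cannot be stated until one censoring rule is chosen. For a true value of 0.50, the illustrations run from about 0.19 (last-scan censoring, half of event-free patients unscanned) to 0.63 (last-contact censoring, mean delay of 12 months). These figures rest on assumed exponential event times, assumed delays and assumed scan patterns. They show how far the estimate can move and do not predict what this trial will report.

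The textual findings need no assumptions: imaging-only progression, no timed scan after surgery, death present in one section and absent from the other, and conflicting censoring dates. The sponsor should correct this while follow-up data can still be collected uniformly. It concerns a secondary endpoint, and the pCR decision rule is unaffected.

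**What to change.** 1. In both Section 12.5 and Section 12.8.2, define the event as first recurrence or progression documented by imaging, endoscopy, biopsy or clinical examination, or death from any cause, whichever is earlier.
2. In the disease-status eCRF field, record the method, date and result of each disease assessment, including standard-of-care scans.
3. Replace the conflicting text with one censoring rule: the last documented disease assessment, counting the three-monthly disease-status visit and not only scans. Add a sensitivity analysis that censors at the last scan. Last-scan censoring should not be the main rule while scans are untimed, because of the downward bias in Case B.
4. If it can be done without extra scans, state the common timing of the standard-of-care imaging in Table 1. Otherwise report scan frequency by site and present 3-year PFS as descriptive, without comparison with historical rates.

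**Cost.** Items 1 to 3 need changes to two paragraphs, an expanded eCRF field and slightly more data entry. Some events will rest on non-imaging evidence, which is why the method should be recorded. Item 4 may not be free: Section 17 gives no number or timing of scans, so naming visits could add procedures, or make them trial-specific and shift their cost to the Principal Investigator. For that reason it is conditional.

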### Patient enrolment

The patient is considered as enrolled when informed consent has been signed by the patient.

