## Protocol deviations and analysis sets

All the deviations from protocol definitions will be listed and defined as major or minor deviations in the SAP.

According to the proposed analysis, the definition of analysis sets is recommended as follows:

- - 1. ITT set: all patients who received at least one administration of the IMP.
    2. Modified ITT Set (MITT): all ITT patients who received at least one administration of IMP, with (the baseline) assessment available and have undergone surgical resection. When further restrictions/qualifications are suggested, they must be specified in a protocol amendment.
    3. Full-Analysis Set (FAS): all patients who received at least one administration of IMP.
    4. Total Treated Set: all patients who received at least one administration of IMP.
    5. Per Protocol (PP) Set: all MITT patients without major deviations. These major deviations must be defined in the protocol or in the SAP.

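### PFS measured from consent in the MITT and PP sets is conditional on reaching surgery, so those two 3-year estimates are probably biased upward

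*Protocol*

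**What the plan says.** **Time origin.** Section 12.8.2: "PFS will be defined for all patients regardless of their pCR as the time between the date the patient is enrolled in the study". The interval ends at progression on imaging or death, whichever comes first, with censoring at the last progression assessment otherwise. Section 8.1.2 fixes enrolment: "The patient is considered as enrolled when informed consent has been signed by the patient". The missing-data rules in section 12.5 repeat this origin: "the date the patient signs the informed consent and is enrolled in the study".

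**Analysis sets.** Section 12.4 defines:
- ITT: "ITT set: all patients who received at least one administration of the IMP". Section 8.2 puts the first dose at D15, two weeks after radiotherapy starts on D1.
- MITT: patients with at least one dose, "with (the baseline) assessment available and have undergone surgical resection".
- PP: "Per Protocol (PP) Set: all MITT patients without major deviations".

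**Sets used for PFS.** Section 12.8.2: "PFS will be analyzed for the ITT, the MITT and the PP set". For MITT and PP the protocol gives no landmark, delayed entry or surgery-based origin.

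**Timing.** The synopsis and Table 1 place surgery at week 16 or 17, counted from the start of radiotherapy, which itself follows consent. After the inclusion imaging, the only imaging scheduled up to surgery is a pelvic MRI, which section 8.2.5 makes optional.

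**The concern.** Membership of MITT and PP is decided by something that happens about four months after the PFS clock starts. A patient who dies in that period, or progresses so that resection is not possible, never enters either set. For those who do enter, the same period is counted as time at risk although they had to get through it to be included. This is immortal-time bias arising from selection on a later event.

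The 3-year progression-free proportion is the first secondary objective (section 2.2), and section 9.2.3 expects it to improve on historical controls. In a single-arm trial the estimate itself is the evidence, so a set that removes early failures makes the regimen look better than it is. MITT is also the primary efficacy set for pCR (sections 12.6 and 12.8.1), which makes it a natural set to quote for PFS too.

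**Working it through.** **1. The plan's own figures.** The protocol states no PFS target, hypothesis or sample size, so there is no PFS figure to reproduce. The enrolment figure does reproduce. Section 12.2 needs 36 patients eligible for the primary analysis and allows for 15 to 20% who are not: 36/0.85 = 42.4, rounded up to 43, and 36/0.80 = 45. The planned 44 lies between. It leaves 44 − 36 = 8 patients outside MITT, or 8/44 = 18.2%.

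The pCR rule also reproduces: early termination at 16% is 65.37% as stated in section 4, the exact type I error is 0.043, and power at 35% is 0.801. None of these depends on PFS.

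**2. Inputs for the size of the effect.**
- 3-year PFS from enrolment, S₃ = 0.50. This is an assumption: section 1.1 gives about 50% for 3-year DFS as disease background, and it is used here as a stand-in. Values of 0.60 and 0.70 are also tried.
- Time from clock start to surgery, t = 15 to 17 weeks. The interval from consent to D1 is not stated and is ignored.
- Months = weeks × 7 / 30.44.

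**3. Constant hazard, with entry requiring patients to be event-free at surgery.** The resected-only 3-year figure is

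S₃ / S(t) = S₃^(1 − t/36), with t in months.

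| Surgery at | t (months) | True 3-year PFS | Resected-only | Excess (points) |
|---|---|---|---|---|
| 15 weeks | 3.45 | 50% | 53.4% | 3.4 |
| 16 weeks | 3.68 | 50% | 53.7% | 3.7 |
| 17 weeks | 3.91 | 50% | 53.9% | 3.9 |
| 16 weeks | 3.68 | 60% | 63.2% | 3.2 |
| 16 weeks | 3.68 | 70% | 72.6% | 2.6 |

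At 50% and 16 weeks this implies that 1 − 0.50^(3.68/36) = 6.8% of patients have an event before surgery. Median PFS from enrolment moves from 36.0 to 36.0 + 3.7 = 39.7 months.

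**4. Without a hazard assumption.** Suppose k of the 8 patients outside MITT had an early event and the other 8 − k do as well as MITT patients. Then 44 × S₃ = q × (44 − k), so q = 44 × S₃ / (44 − k). At S₃ = 0.50:

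| k | MITT 3-year PFS, q | Excess (points) |
|---|---|---|
| 0 | 50.0% | 0 |
| 2 | 52.4% | 2.4 |
| 4 | 55.0% | 5.0 |
| 6 | 57.9% | 7.9 |
| 8 | 61.1% | 11.1 |

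**5. The ITT set.** The same formula with t = 2 weeks (0.46 months) gives 0.50^(1 − 0.46/36) = 50.4%, an excess of about 0.4 points.

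**The case against.** - **An analysis that does not depend on surgery is already planned.** ITT is listed first for PFS and does not require resection. Section 12.2 says the larger enrolment may improve the precision of PFS, which makes sense only if PFS rests on a set larger than the 36 MITT patients. This stands, and it limits the damage. It does not correct the MITT and PP analyses, which are ordered in the same sentence without being described as conditional.
- **A reader might infer that all pre-surgical time is event-free by construction.** That is strictly true only for death. Progression seen on the optional pre-surgical MRI is a PFS event and can still be followed by resection. With no other imaging scheduled in that period, the statement is nearly true for progression, but not entirely.
- **A reader might infer that the bias must be upward.** That requires patients who miss surgery to do worse. If they miss it for reasons unrelated to prognosis the bias tends to zero, and it could reverse if good responders decline surgery. Upward is the probable direction, not a certain one.
- **A reader might take 15 to 20% as the share who never reach surgery** and compute 0.50/0.85 = 58.8% to 0.50/0.80 = 62.5%. The synopsis and section 12.2 do not say that. The percentage covers every reason for ineligibility, including no dose or no baseline assessment, and patients without a dose are outside ITT as well.
- **A reader might object that no lead PFS set is named.** That is commonly settled in the SAP, which is not shown, so it is not held against the protocol.
- **Constant hazard from consent is not supported by the documents.** With so little imaging before surgery, few progressions may be recorded in that period. This stands, and is why the result is given as a range.

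**Conclusion.** The point holds as a defect in two of the three planned PFS analyses. As written, the MITT and PP estimates describe patients who reached surgery but are measured from consent, and they are probably too high.

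The excess is about 3 to 4 points on a 3-year rate of 50% under constant hazard, and anywhere from 0 to about 11 points depending on how many of the 8 patients expected outside MITT fail early. Both figures rest on borrowing a background DFS rate for PFS. The upper end is an extreme case in which all 8 have early events.

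The ITT estimate is largely free of the problem, at about 0.4 points. A reader might infer that the trial's main conclusion is at risk. It is not: PFS is secondary, section 12.8.2 attaches no hypothesis or test to it, and the pCR test and sample size do not change. The correction is still worth making because the 3-year rate is likely to be read against historical results.

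**What to change.** 1. In section 12.8.2, start the PFS clock for MITT and PP at the date of surgery and label the result a landmark analysis, conditional on resection. State how a patient with progression imaged before surgery is handled. Alternatively, drop MITT and PP for PFS.
2. Rest the 3-year PFS rate on the set that does not require surgery.
3. If that set is widened to everyone who started radiotherapy, start its clock at D1, so that set entry and time origin coincide. Keeping the consent clock there would repeat the problem on a smaller scale.
4. Bring the restated time origin in section 12.5 into line.

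The cost is wording in the protocol and SAP. Consent, radiotherapy, dosing and surgery are protocol procedures whose dates the trial already records, so no new data are needed. The downside is that the resected-only figure is no longer comparable with a figure measured from enrolment, and the two should not be shown side by side as if they were.
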